**General principles**

- This analysis plan and the primary manuscript will include clinical data up to 90 days, transcriptomic and cell population (by flow cytometry) analyses; the entire cost-effectiveness analysis, cytokine analysis (including serum cytokine concentrations and cytokine production from supernatants of ex-vivo stimulated peripheral blood mononuclear cells-PBMCs) and microbiome analysis will be reported separately.
- Regarding flow cytometry analysis (including cell population and HLA-DR analysis), only samples from patients enrolled in sites proximal to the central lab (Athens) could be included in the current study.
- Regarding trasncriptomic analysis, only a subset of sample sequencing could be covered by the study funding at the time of the present statistical analysis plan. Thus, it was decided to only include in the primary manuscript samples from the subgroup of patients of extremely high severity (within the highest quartile of baseline SOFA score), to demonstrate differences between death and survival. The entire transcriptomic analysis, combined with metabolome, cytokine and microbiome analysis will be reported separately.
- All p-values will be two-sided and the level of significance will be <0.05.
- No interim analysis is planned.
- Regarding clinical data, cell populations and HLA-DR measurements, no adjustment for multiple comparisons is planned and all secondary outcomes will be viewed as exploratory. For transcriptomic data, statistically significant differences will be defined by Benjamini & Hochberg adjusted probabilities < 0.05 and absolute fold expression ≤−1.5 or ≥1.5.
- Analyses will be conducted primarily by the SPSS statistical software, version 24 (IBM) or later; transcriptomic data twill be analysed in the R statistical framework (Version 3.51, R Core Team 2014. R: A language and environment for statistical computing. R Foundation for Statistical Computing, Vienna, Austria)
- Results will be presented by order of importance, starting with the primary outcome first. Due to the nature of the study, additional exploratory analyses will be performed based on the primary and secondary outcomes, in an effort to identify potential host immune pathways modulated by the study drug.

**Descriptives and baseline comparisons**

- Categorical variables will be expressed as counts (and percentages), providing the number of patients or events entered at every step of the analysis.
- The Kolmogorov-Smirnov test for normality will be conducted to the entire population and the arms of study intervention. Continuous variables with normal distribution will be presented with their mean and standard deviation (SD), those with a skewed distribution will be presented with their median and quartiles (Q1-Q3).
- The following variables will be compared among study groups:
  - **Severity and demographics.** Age at inclusion, gender, weight, (enrollment) acute pathophysiology and chronic health evaluation (APACHE) II score, (enrollment) Charlson Comorbitdy Index (CCI), baseline SOFA score (identified as the worst SOFA within any 24h between screening and randomization), sepsis start date, infection start date, time (days) from hosital admission to enrollment, ARDS at enrollment, mechanical ventilation at enrollment, septic shock at enrollment, laboratory data (the most abnormal value within the last 24h prior to enrollment), microbiological data (from infection start).
  - **Concomittant treatment,** including all medication, including inotropic, antimicrobial, fluids and blood products received at enrollment. Medication througout 28 days will be assessed for cost-effectiveness analysis.
  - **Adequacy** of antimicrobial treatment will be defined as susceptibility of the identified pathogen (if any) to the empirical treatment given 48h after sepsis start, with optimal dosing and penetration to infection site.

**Analyses for the primary outcome**

The primary outcome will be assesed on an intention-to-treat (ITT) basis, as a 2x2 contigency table by the Fischer’s exact test, and will be confirmed by logistic regression analysis, adjusted for the following severity variables: Age, gender, CCI, SOFA, APACHE II and adequacy of empirical antimicrobial treatment. In case of high collinearity between the model variables, such as age and APACHE, age and CCI or APACHE and SOFA (assessed by the variance inflation factor-VIF, and correlation), if VIF>2 or Pearson correlation coefficient ≥0.8, then only the variable with the lowest p-value in the univariate regression analysis will be entered in the multivariable model. Multivariable regression analysis will be performed in a forward step-wise manner.

Moreover, the rate of incidence of the primary outcome will be compared between the two arms by the log-rank test and the effect size will be quantified by Cox-regression analysis. Finally, the mean absolute difference in mortality among treatment arms will also be presented, with respective 95% CI and the z-statistic for significance.

- Subgroup analyses, with regards to the primary outcome, are planned according to all the subpopulations identified, as follows: per country; per ward of enrollment (ICU or general ward); per protocol (according to whether the study intervention was complete -all 4 doses received); per presence of septic shock (already present in the protocol); per highest SOFA score (defined as higher or lower than the upper SOFA quartile of the population); per presence of ARDS; per initial infectious site; per adequacy of empirical antimicrobial treatment; and per Gram-negative vs non-Gram negative pathogen, among infections with identified pathogens. Interactions between subgroups and arm of treatment were assessed with Breslow-Day test and confirmed with logistic regression for the primary outcome.

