Primary Gram-negative bacteremia (BSI) is defined as the isolation of at least one Gram-negative microorganism from a blood culture of a peripheral vein of a patient that is not related to infection of a central line and who presents with ALL the following features^16^:

- Core temperature equal or greater than 38°C or total white blood cell count more than 12,000/mm^3^
- Thorough clinical and radiological investigation has failed to identify the primary infection site

Intra-abdominal infection (IAI) is defined as the presence of ALL the following features^16^:

- Core temperature equal or greater than 38°C or total white blood cell count more than 12,000/mm^3^
- Radiological findings from abdominal ultrasound or abdominal computed tomography or magnetic resonance imaging consistent with one IAI or peri-operative confirmation of an IAI.

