**Populations**

Analyses will be performed on an intention-to-treat (ITT) basis, including all randomized patients, independently of wheather they received the sudy intervention. The ITT population will enter analysis of the primary and all secondary outcomes. In case of consent withdrawal, all data collected prior to this point will be excluded.

The following subgroups of patients are potentially identified:

- Enrolled inside and outside of the intensive care unit (ICU)
- Enrollement in Greece and in Belgium
- Presence or absence of septic shock
- Presence or absence of acute respiratory dysfunction syndrome (ARDS)
- Extremely high severity, defined as patients within the highest quartile of SOFA score, vs all others.
- Presenting pneumonia, intra-abdominal infection or primary Gram-negative bacteremia
- Presence or absence of a Gram-negative pathogen (among infections with identified pathogen only)
- Adequate vs non-adequate empirical antimicrobial treatment (among infections with identified pathogen only). Empirical antimicrobial treatment (defined as the regimen given within 48 hours from infection onset, when cultures are pending) is considered as adequate when administered at the indicated dose and with penetration to the infected site; provided that the identified pathogen has documented or reasonably suspected susceptibility (e.g. metronidazole for *Clostridioides difficile* infection)
- Per protocol (PP) population, defined by patients receiving the entire intervention (all 4 daily doses)

Subgroup analyses will be performed for mortality outcomes (28-day and 90-day).

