**Missing values**

Missing values will be treated as such, and the number and percentage of patients or events entering each step of the analysis will be provided. The Little’s test will be used to assess whether missing values are missing completely at random.

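### The adjusted logistic model meant to confirm the primary result is not guaranteed to contain treatment and, under a standard fit, leaves out randomised patients with no identified pathogen

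*Supplement*

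**What the plan says.** The SAP section Analyses for the primary outcome makes the ITT comparison the main test: "The primary outcome will be assesed on an intention-to-treat (ITT) basis, as a 2x2 contigency table", by Fisher's exact test. A logistic regression is then to confirm it, "adjusted for the following severity variables: Age, gender, CCI, SOFA, APACHE II and adequacy of empirical antimicrobial treatment". If two covariates are highly collinear (VIF above 2 or correlation of at least 0.8), "then only the variable with the lowest p-value in the univariate regression analysis will be entered in the multivariable model". The paragraph ends: "Multivariable regression analysis will be performed in a forward step-wise manner". The same section adds a log-rank test, a Cox effect size and the absolute mortality difference with a confidence interval.

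Adequacy is described twice. SAP, Populations, lists the subgroup "Adequate vs non-adequate empirical antimicrobial treatment (among infections with identified pathogen only" and counts the regimen given in the 48 hours from infection onset. SAP, Descriptives and baseline comparisons, defines adequacy as "susceptibility of the identified pathogen (if any) to the empirical treatment given 48h after sepsis start".

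SAP, Missing values, gives this rule: "Missing values will be treated as such, and the number and percentage of patients or events entering each step of the analysis will be provided". SAP, Populations, says that all randomised patients enter the primary-outcome analysis.

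**The concern.** Adjusting for a fixed list and building a model by forward steps are different procedures, and the SAP prescribes both for one model. Nothing exempts treatment from selection, so the model that is to confirm the primary result may contain no treatment term. If an adjusted estimate is reported only when treatment enters, reporting becomes selective. Choosing adjusters on the trial's own outcome data also makes the model depend on those data, and the usual standard error ignores this.

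Adequacy has no stated value when no pathogen is found, yet such patients are eligible. With missing values left missing, ordinary regression software drops them. The confirmatory model would then describe a subset defined by microbiology and not the ITT population, and could differ from the Fisher test because it covers different patients.

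The two adequacy definitions use different clocks. The eligibility criteria set no limit on the time from onset to randomisation, so either window may extend past it, which would make adequacy partly a post-randomisation variable.

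**Working it through.** **1. Can a randomised patient lack an adequacy value?** Protocol version 2, Definitions, sets the entry routes:
- Pneumonia (HAP, HCAP, VAP) needs an infiltrate plus two features from a list. A Gram stain result is only one optional feature.
- Intra-abdominal infection needs a temperature or white-cell criterion plus "Radiological findings from abdominal ultrasound or abdominal computed tomography or magnetic resonance imaging consistent with one IAI or peri-operative confirmation of an IAI". No isolate is needed.
- Primary Gram-negative bacteremia does require an isolate.

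So patients without a pathogen can be enrolled, and whether adequacy is missing is tied to infection type. Neither adequacy definition assigns them a value, and SAP, Missing values, gives no imputation or extra category.

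**2. The plan's own sample size.** Protocol version 2, Power calculation: 55% vs 30%, type I error 0.10, power 0.80, 1:1. With p̄ = 0.425 and Δ = 0.25:

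n = [1.645·√(2·0.425·0.575) + 0.842·√(0.55·0.45 + 0.30·0.70)]² / 0.25² = 47.3 (48 rounded up).

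Continuity-corrected: (n/4)·[1 + √(1 + 4/(nΔ))]² = 55.0. The stated 55 per arm is reproduced, so the same rates are used below. Expected deaths: 55·0.55 + 55·0.30 = 46.75, about 47.

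**3. What exclusion costs.** The share without an identified pathogen is not in the documents; 20-50% is assumed. Unadjusted two-proportion power at the SAP's two-sided 0.05:

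power = Φ{[Δ − 1.96·√(2p̄(1−p̄)/n)] / √([p₁(1−p₁) + p₂(1−p₂)]/n)}

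- n = 55: (0.25 − 0.1848)/0.0912 = 0.715, Φ = 0.763
- n = 44: (0.25 − 0.2066)/0.1020 = 0.426, Φ = 0.665
- n = 27.5: (0.25 − 0.2613)/0.1290 = −0.088, Φ = 0.465

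| No pathogen (assumed) | Patients left | Expected deaths | Power |
|---|---|---|---|
| 0% | 110 | 47 | 0.763 |
| 20% | 88 | 37 | 0.665 |
| 30% | 77 | 33 | 0.605 |
| 40% | 66 | 28 | 0.539 |
| 50% | 55 | 23 | 0.465 |

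Deaths are patients × 0.425, assuming mortality unrelated to pathogen identification. The power figures are for an unadjusted test; they show the scale of the loss and are not the power of the logistic model.

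**4. How often forward selection leaves treatment out.** The SAP gives no entry threshold; likelihood-ratio entry at 0.05 was assumed. Each simulated trial had 110 patients and six covariates. Assumed log-odds effects were 0.3 (age), 0.2 (CCI), 0.5 (SOFA), 0.3 (APACHE II, correlated with age and SOFA), 0 (sex) and −0.5 (adequacy, 75% adequate). There were 600 trials per setting, and patients were lost at random.

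| Mortality | None lost | 30% lost | 50% lost |
|---|---|---|---|
| 55% vs 30% | 20% | 36% | 53% |
| 55% vs 40% | 59% | 70% | 76% |

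A separate simulation with other assumed effects gave 19% and 63% with no loss.

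**5. Is that a loss of power?** In a further run of 1,500 trials, non-entry was compared with non-significance of treatment in a model with everything forced in: 20% against 18% at 55% vs 30%, and 59% against 56% at 55% vs 40%. The two approaches agreed on significance in 94-96% of trials. Entry at 0.05 is nearly the same event as significance at 0.05.

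**The case against.** The strongest reply is that the phrase about adjustment makes treatment the exposure and the six variables the adjusters, so stepwise selection was meant for the adjusters only. That reading is possible. However, the SAP does not say so, and Protocol version 2, Statistical analysis, describes logistic regression as a search for variables linked to 28-day mortality, which fits the other reading. Even on the charitable reading, the adjusters are still chosen by p-value.

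Several stronger claims are tempting, and the documents do not support them:
- *Patients vanish silently.* SAP, Missing values, promises the number entering each step, so the loss would be visible.
- *The SAP prescribes deletion.* It does not. Deletion is inferred from the adequacy definitions and the missing-value rule together, and a separate no-pathogen level is not ruled out.
- *All covariates are screened univariately.* The univariate p-value decides only between collinear variables.
- *Stepwise selection itself exaggerates the treatment effect.* At 55% vs 40%, the simulated median odds ratio was 0.30 when treatment entered, and also 0.30 in the forced model restricted to its significant trials; the forced model gave 0.44 over all trials. The exaggeration comes from looking only at significant results. It arises here only if estimates that do not enter go unreported.
- *The primary conclusion is at risk.* Fisher's test, the log-rank test and the risk difference use neither stepwise selection nor adequacy.
- *The adequacy windows bias the result.* No bias is shown, and everyone except the study pharmacist is blinded, so arm should not drive antibiotic choice.

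**Conclusion.** The point holds, limited to one supporting model. As written, the adjusted analysis labelled as confirming the ITT result may report no treatment estimate. Under a standard fit it would also cover only patients with an identified pathogen. Its adequacy covariate has two time windows that must be reconciled.

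On the assumed 20-50% without a pathogen, 22 to 55 of 110 randomised patients would drop out of the model. The omission rates (roughly 20% at the design effect, about 60% at 55% vs 40%) depend on the assumed covariate effects and entry threshold and are illustrative. They mean a missing or selectively reported adjusted estimate, not a large loss of power from stepwise selection. This should be fixed, but it does not undermine the primary test.

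**What to change.** Replace the logistic specification with: logistic regression in all randomised patients with an available 28-day outcome, treatment arm forced in, and age, sex, CCI, baseline SOFA and APACHE II all entered, with no stepwise, univariate or VIF-based selection. Collinearity among the adjusters does not harm the treatment coefficient, so the VIF rule is not needed here. Report the treatment odds ratio and its confidence interval whatever the p-value.

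For adequacy, either move it to a sensitivity analysis or code it as adequate / inadequate / no pathogen identified. Use one reconciled definition, based on antimicrobials given before randomisation.

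The cost is SAP wording. The variables are already collected, and the SAP is dated before unmasking and database lock. There is a small downside: about 47 expected deaths support 6 parameters (treatment plus five covariates) or 8 with three-level adequacy, i.e. 47/6 = 7.8 or 47/8 = 5.9 deaths per parameter.

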**Analyses for secondary outcomes**

The effect of the study arm on secondary outcomes will be compared with the Pearson chi-square test, or the two-sided Fisher’s exact test for 90-day mortality, early sepsis response and sepsis resolution, as well as new sepsis incidence. Clinical secondary outcomes will be evaluated on an ITT basis.

- Regarding 90-day mortality, the following subgroup analyses are planned (for all subpopulations identified): per country; per ward of enrollment (ICU or general ward); per protocol (according to whether the study intervention was complete -all 4 doses received); per presence of septic shock (already present in the protocol); per highest SOFA score (defined as higher or lower than the upper SOFA quartile of the population); per presence of ARDS; per initial infectious site; per adequacy of empirical antimicrobial treatment; and per Gram-negative vs non-Gram negative pathogen, among infections with identified pathogens. Interactions between subgroups and arm of treatment were assessed with Breslow-Day test and confirmed with logistic regression for the primary outcome.
- The time to new sepsis incidence will be compared only for patients experiencing a new sepsis episode both by the Mann-Whitney test, and as Cox-regression analysis of the treatment effect on the time to new sepsis episode, with death as competing event.
- Cell populations and monocytic HLA-DR variables will be assessed using Student’s t-test (for variables following a normal distribution), Mann-Whitney U (for variables following a skewed distribution), as appropriate. Overtime changes will be assessed by the k-related samples non-parametric Friedman test, separately per study arm, and the mixed ANOVA test with time and study arm as within-subject and between-subject factors respectively.
- Transcriptomic data wil be illustrated by Volcano plots for differential expression of genes among study groups, while gene set enrichement analysis will also be performed to identify pathways of transcriptomic changes among study groups. Any need for additional (post-hoc) analyses will be re-evaluated. Functionality of differentially expressed transcripts will be assessed by the ENCODE project.

Raw sequence data and count data will be uploaded on National Center for Biotechnology Information (NCBI) gene expression omnibus (GEO), to be publicly available.

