***Study visits***

*Screening visit*

When a patient meets ALL inclusion criteria and NONE of the exclusion criteria, he/she can be enrolled in the study. The criteria are judged based on data available from the patient’s file. Female patients of reproductive age should be screened with a urinary pregnancy test. QT prolongation or prior arrhythmia is not considered as an exclusion criterion for the study, ^9,11^ but may be considered in the decision making of the principal investigator. The same patient cannot be enrolled twice in this study.

*Patient follow-up*

Follow-up of every patient will be done daily until day 28 or hospital discharge (whatever comes first).

Visit 1 is on day 1. Procedures of this day include:

- Recording of demographics, medical history, co-morbidities (Charlson Comorbidity Index), ^17^ SOFA score (see APPENDIX II); Acute Physiology and Chronic Health Evaluation (APACHE) II score (see APPENDIX III), available blood cell count, biochemistry, coagulation time, urine output, blood gas analysis, recording of suspected infection site, available radiological findings, relevant for the current infection microbiology and antimicrobial susceptibility testing if available, administered antimicrobials, other administered drugs and need for source infection control either by percutaneous interventions or by any operation.
- Sampling of 35 ml of venous blood; 3ml is collected into one PAXgene tube or a tube with RNA*later*®; 9ml is collected into one pyrogen-free tube; and 24ml is collected into EDTA-coated tubes
- Collection of stool culture or rectal swab
- Administration of the study drug
- Evaluation of potential adverse events

Visit 2 is on day 2. Procedures of this day include:

- Recording of SOFA score (see APPENDIX II); available blood cell count, biochemistry, coagulation times, urine output, blood gas analysis, available radiological findings, relevant for the current infection microbiology and antimicrobial susceptibility testing if available, administered antimicrobials, other administered drugs and need for source infection control either by percutaneous interventions or by any operation.
- Survival status
- Administration of the study drug
- Evaluation of potential adverse events

Visit 3 is on day 3. Procedures of this day include:

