**STATISTICAL ANALYSIS**

Qualitative endpoints will be analyzed by the Fisher’s exact test or continuity corrected Chi- square test, as appropriate. Logistic regression models will be used to evaluate variables associated with 28-day mortality. The effect on sepsis-induced immunosuppression will be a composite endpoint and it will result from the bioanalysis of gene expression, circulating cytokines and stimulated cytokines of patients. More precisely, bioanalysis of gene expression is anticipated to provide pathways modulated by treatment. These pathways will be validated by measurement of representative cytokines in cell supernatants. Comparisons of over-time changes will be done between the two groups of treatment. A p - value lower than 0.05 will be considered statistically significant, unless stated otherwise.

For the cost analysis, cost of each intervention will be counted and compared between groups, with non-parametric Mann-Whitney test, as previously described^10^. This analysis will be subject to robustness control to assess potential differences between different methods of cost calculation. Cost-effectiveness will be expressed as an incremental cost-to-effectiveness ratio (ICER) of clarithromycin compared with placebo, in a within-trial analysis (90 days). The ICER will be compared to a willingness-to-pay factor, which is either defined by the National Institute for Health and Care Excellence threshold or by per capita Gross Domestic Product. ^19, 20^

To evaluate the variation and significance of the ICER estimate, a bootstrapping method will be used.

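### The SAP plans only a crude 2×2 test, with no overall effect estimate or interval, for 90-day mortality and the two SOFA-response endpoints, although the baseline severity variables it uses elsewhere are available for adjustment

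*Supplement*

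**What the plan says.** SAP, Analyses for secondary outcomes: "The effect of the study arm on secondary outcomes will be compared with the Pearson chi-square test". A two-sided Fisher test is the stated alternative. The endpoints covered are mortality at day 90, the two SOFA responses and new sepsis episodes. No covariates, effect measure or interval are named for the overall comparison. Regression appears in the 90-day bullet only for subgroup interactions, and the wording there refers to the primary outcome.

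SAP, Analyses for the primary outcome: 28-day mortality is tested by Fisher's exact test. A confirmatory logistic model follows, "adjusted for the following severity variables: Age, gender, CCI, SOFA, APACHE II and adequacy of empirical antimicrobial treatment", and "Multivariable regression analysis will be performed in a forward step-wise manner". The same section adds that "the effect size will be quantified by Cox-regression analysis", and promises an absolute mortality difference with a 95% CI. All of this sits under the primary outcome.

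Protocol version 2, Statistical analysis: "Logistic regression models will be used to evaluate variables associated with 28-day mortality". This too is limited to day 28.

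Protocol version 2, Study visits, Visit 1, lists "Recording of demographics, medical history, co-morbidities (Charlson Comorbidity Index" together with SOFA and APACHE II. SAP, Descriptives and baseline comparisons, defines baseline SOFA as the worst score between screening and randomisation. SAP, General principles, sets two-sided 0.05 and calls all secondary outcomes exploratory.

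**The concern.** A 2×2 test of a binary outcome is valid under randomisation, but it treats any variation that baseline severity could explain as noise. Where the covariates predict the outcome, an adjusted analysis is more likely to detect a real effect. It also corrects chance imbalance in severity, against which this design has little protection: allocation is stratified by site only, with 110 patients planned over 13 sites.

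The missing estimate matters as much as the test. These endpoints are exploratory and carry no multiplicity control, so the reader needs an effect size with an interval. The SAP promises one for 28-day mortality and none for these three endpoints.

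**Working it through.** **The plan's own figure.** Protocol, Power calculation: 55% vs 30%, type I error 0.10, power 0.80. Taken as two-sided:

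- Uncorrected n = [1.645·√(2·0.425·0.575) + 0.842·√(0.55·0.45 + 0.30·0.70)]² / 0.25² = 47.3, so 48 per arm.
- With continuity correction, n' = (47.3/4)·[1 + √(1 + 4/(47.3·0.25))]² = 55 per arm. This reproduces the protocol.

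**Inputs for 90-day mortality.** n = 55 per arm (protocol) and two-sided 0.05 (SAP). Two inputs are assumptions, because the documents give neither:

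- 90-day rates of 60% vs 35% (the plan's 25-point difference carried to day 90) or 60% vs 40%.
- The share R² of outcome variance that the covariates explain, taken as 0.05 to 0.30.

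**Formula.** Power = Φ{[d√n − 1.96·√(2p̄q̄)] / √(p₁q₁ + p₂q₂)}, where d is the risk difference. Adjustment is approximated by replacing n with n/(1 − R²).

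For 60% vs 35%, unadjusted: (0.25·7.416 − 1.96·0.706)/0.684 = 0.687, so power is 75.4%. With R² = 0.05, n becomes 57.9 and power 77.6%. With R² = 0.30, n becomes 78.6 and power 88.8%.

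| R² | 60% vs 35% | 60% vs 40% |
|---|---|---|
| 0 | 75.4% | 55.6% |
| 0.05 | 77.6% (+2.2) | 57.8% (+2.2) |
| 0.10 | 79.8% (+4.4) | 60.1% (+4.5) |
| 0.15 | 82.0% (+6.6) | 62.6% (+7.0) |
| 0.20 | 84.3% (+8.9) | 65.3% (+9.7) |
| 0.30 | 88.8% (+13.4) | 71.2% (+15.6) |

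**Loss to follow-up.** With the SAP's 10% loss, 55 × 0.9 = 49.5, taken as 50 per arm. At 60% vs 35% unadjusted power is 71.3%, and the gain is +2.2 at R² 0.05 and +14.4 at R² 0.30.

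**Check by simulation** of logistic models with five fixed covariates and a Wald test, 55 per arm:

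| Rates | AUC of covariates | Fisher | Pearson | Adjusted | Gain over Pearson |
|---|---|---|---|---|---|
| 60% vs 35% | 0.64 | 67.5% | 74% | 78% | +4 |
| | 0.70 | 67.5% | 74% | 80% | +6 |
| | 0.76 | 67.5% | 74% | 83% | +9 |
| | 0.81 | 67.5% | 74% | 87% | +13 |
| 60% vs 40% | 0.66 | 46% | 52% | 57% | +4 |
| | 0.74 | 45% | 53% | 64% | +10 |
| | 0.80 | 46% | 54% | 68% | +14 |

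Gains are taken before rounding. Fisher and Pearson at 60% vs 35% are exact enumerations. At a 60% event rate, AUC 0.66, 0.74 and 0.80 correspond to R² of about 0.08, 0.17 and 0.27. The simulations top out near +14; only the approximation, at R² 0.30 and 60% vs 40%, goes slightly higher.

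**Type I error.** About 5 to 6% for the adjusted Wald test. In one null simulation at 50% in both arms it was 4.9%, against 4.4% for Pearson and 2.6% for Fisher.

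**Room for the model.** At 60% vs 35%, expected deaths are 33 + 19.25 = 52.25. With arm plus five covariates, that is 52.25/6 = 8.7 per coefficient: workable, but not generous.

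**The case against.** **The outcomes are exploratory and the crude test is valid.** True. No confirmatory conclusion depends on its power. This caps the priority, but does not supply the missing estimate and interval.

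**The size of the gain is assumed.** True. Eligibility already requires PaO2/FiO2 below 200 and more than 3 non-respiratory SOFA points. That narrows the severity range, so weak predictors are plausible; at R² 0.05 to 0.10 the gain is only about 2 to 5 points. A reader might infer that most of the variation in death comes from baseline severity. Nothing in the documents shows this, and even R² 0.30 leaves 70% unexplained.

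**Part of the gain is test size.** This stands in part. Pearson runs slightly below 5% here and the adjusted test slightly above. When a likelihood-ratio version with four covariates and Pearson were both calibrated to 5%, at 60% vs 35%, the gain was about 0.5 points at AUC 0.63, 4 at 0.70, 5 to 6 at 0.76 and 14 at 0.82.

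**The loss might be read across to all three endpoints.** The documents do not support that. They give no response rates, and a predictor of death need not predict a 25% relative fall in SOFA. The case for adjustment there is qualitative: day-1 SOFA is the denominator of the response criterion.

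**The main analysis of 28-day mortality might be taken as adjusted.** It is not. The lead test is crude Fisher, and the adjusted model is confirmatory and step-wise. The secondary tests therefore follow the primary's lead method, and the step-wise form is not one to copy.

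**Conclusion.** The gap holds: neither the SAP nor the protocol plans an adjusted analysis, an overall effect estimate or an interval for 90-day mortality, early sepsis response or day-7 resolution, although suitable baseline variables are collected.

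For 90-day mortality the power forgone against Pearson is roughly 2 to 14 points, and more against Fisher, which is conservative. This rests on assumed rates of 60% vs 35% or 60% vs 40%, 55 per arm, two-sided 0.05, and an assumed predictor strength of R² about 0.05 to 0.30 (AUC about 0.64 to 0.81). It is a conditional range, not a figure from the plan. No power figure is claimed for the SOFA responses.

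Priority is low to moderate: this concerns the precision and reporting of exploratory outcomes.

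**What to change.** Before unblinding, add to the SAP section on secondary outcomes a pre-specified logistic model for each of the three endpoints:

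- Terms: arm, age, sex, Charlson index, baseline SOFA (the SAP's pre-randomisation definition) and APACHE II, all fixed in advance with no step-wise selection.
- Leave out adequacy of empirical antimicrobial treatment, which exists only where a pathogen is identified.
- Report the standardised (marginal) risk difference with 95% CI.
- Keep the Pearson or Fisher test as a sensitivity analysis.

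The cost is some SAP wording and a few lines of code, with no new data. The downside is modest dependence on the model and a type I error of about 5 to 6% at this sample size.
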